### Interventions

#### Internet-delivered psychological intervention

All interventions (except iTAU) comprise two face-to-face individual sessions and 6 online, individual and interactive therapeutic modules. Each face-to-face session will be 90 min in length. The online therapeutic modules are oriented to work on different psychological techniques, supported by multimedia material (videos, audio, etc.), as Internet support, and the duration of each module will be approximately 60 min.

The content of the modules is explained in depth later. The structure of the modules always follows the same scheme: each begins with the explanation of the contents of the module, different exercises are proposed, and then the self-test questions are presented to verify whether the explanation has been understood. If any user does not correctly answer any question, the computer program will immediately provide the correct feedback with a simple explanation. The module ends with the proposal of homework with the aim of practising what has been learned. In addition, before starting each module, a check is made to see whether the participants have carried out the proposed tasks and responds by congratulating them or encouraging them to do the task. It is very important to carry out these tasks in order to consolidate everything learned in the programme and so that the strategies offered by the programme are turned into skills. An important aspect is the possibility of reviewing the content of the different modules. The programme is designed to last 8–12 weeks. After some time without accessing the computer program (a time that can be programmed), the user will receive a reminder e-mail to continue completing the modules. The clinician can modify the period that should pass without entering to receive said reminder. The programme contents are the following:*Face-to-face session 1. Presentation of the programme:* Motivational techniques will be used to increase adherence of participants to face-to-face sessions and homework, and adherence to pharmacological treatment will be also promoted as one of the main focal points of the programme. The online computer program will be presented and patients will be trained in the procedure to log in and use it from home.*M1. Psychoeducation of depression:* The impact of depression on patients’ quality of life and functional ability, as well as on the prognosis of diabetes and other chronic diseases, will be described. The initial symptoms of depression and how to respond when they appear will be analysed. Self-control under stress will be emphasized, with patients taught to do relaxation exercises and to reward efforts and achievements made. In addition, specific techniques and very useful and practical tips to reduce stress in daily life will be explained.*M2. Healthy Life Style*: The need to carry out regular physical activity will be explained. The Mediterranean diet will be introduced, with education on the need to follow 6 healthy dietary commands. All of this will come with information and practical exercises on how to systematize food-related behaviours. Developing a social support network will be emphasized. People will be shown specific techniques on how to create and maintain an adequate social support network.*M3. Behavioural activation:* The importance of establishing and maintaining an adequate level of activity and involvement with life will be considered. Patients will be taught to schedule activities, and the need to monitor the performance of significant activities will be explained. The essential tool of this module will be the ‘Activity Diary’.*M4. Positive psychology:* This module will help patients to see the importance of positive emotions and learn procedures that generate positive experiences, encouraging involvement in pleasant and meaningful activities and contact with other people.*M5. Mindfulness and compassion*: This module will include components of Mindfulness-based Cognitive Therapy (MBCT). Core mindfulness practices will be carried out: the practice of breathing, the body scan and the 3-min exercise. The importance of establishing a regular mindfulness practice, as well as regular informal practice, will be considered. Some basic elements of compassion will be included, such as the self-compassionate pause.*Face-to-face session 2. Review of completed modules already and practice*. This is a structured session comprising: a) resolution of doubts, b) performing some of the most important practices (proposed to be done periodically at home), c) emphasizing the continuous putting into practice of the strategies learned and d) farewell and intervention closure.*M6. Relapse prevention and maintenance*: This module aims to strengthen the strategies learned during the programme. The possibility of continuing to practice the strategies learned once the treatment is completed will also be discussed, with emphasis on the fact that participants can continue to use the online computer program during the entire follow-up period (6 months) for this purpose. It will also teach participants how to identify and cope with future high-risk situations. Finally, instructions will be given to conduct follow-up evaluations.

This group of patients will also receive iTAU from their GPs, as described in the next paragraph.

#### iTAU at primary care level

All the patients included in the study (whether they receive the Internet-delivered psychological intervention or not) will be also treated by their GPs. In practice, treatment-as-usual in PC is any kind of treatment administered by the GP to the patient with depression. However, this treatment in primary care will be improved because the participating GPs will receive a training programme on the widely used Spanish Guide for the Treatment of Depression in Primary Care, which is based on the NICE guidelines on subject [15]. In case of suicide risk, severe social dysfunction or worsening of symptoms, it is recommended that patients are referred to mental health facilities [38]. For both groups, the use of health and social services – including consultations with professionals, pharmaceutical use and other resources, will be registered using the Client Service Receipt Inventory (CSRI) [39].

### Instruments

The assessor will be blind to the type of treatment that will be administered to patients. In addition, this assessor will be different from the person who collects the measurements of the study results. As far as possible, GPs will also be blind to the intervention arm to which each patient is allocated, since their intervention should be based only on usual practice, based on the criteria set out in the Guide for the Treatment of Depression in Primary Care.

Patients will be assessed at baseline (post-randomization), after the treatment, and at 3-month and 6-month follow-ups, in order to test whether the improvements achieved during the therapy are maintained in the long term. The study variables assessed are summarized in Table 2. The study flowchart is shown in Fig. 1.

**Table 2 Tab2:** Study variables

Instrument	Assessment area	Time to assessment	Applied by
PHQ-9 (40, 41)	Severity of depression	Baseline and follow-up sessions^a^	Researcher A phone Online (follow-up sessions^a^)
Glycosylated haemoglobin	Diabetes control	Baseline and follow-up sessions^a^	Online
FPS-R [42]	Pain intensity	Baseline and follow-up sessions^a^	Online
Roland-Morris Scale [43–46]	Physical limitation	Baseline and follow-up sessions^a^	Online
MINI [47]	Psychiatric diagnosis	Baseline	Researcher A phone
Sociodemographic data	Gender, age, marital status, education, occupation, economical level	Baseline	Researcher A phone
SF-12 Health Survey [48, 49]	Health-related quality of life	Baseline and follow-up sessions^a^	Online
CRSI [39, 50]	Health and social services use	Baseline and 6 months post-treatment	Researcher A phone (Baseline) Researcher B phone (6 months post-treatment)
EQ-5D-3 L [51, 52]	Quality of life related to health	Baseline and follow-up sessions^a^	Online
OFS [53]		Baseline and follow-up sessions^a^	Online

*PHQ-9* Patient Health Questionnaire, *FPS-R* Faces Pain Scale –Revised, *MINI* Mini-International Neuropsychiatric Interview, *CSRI* Client Service Receipt Inventory, *EQ-5D-3 L* EuroQol-5D-3 L, *OFS* Openness to the Future Scale

^a^Follow-up sessions: post-treatment, 3 and 6 post-treatment months

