### Setting and study sample

Participants will be recruited from PC health centres in the three Spanish regions participating in the study (Andalusia, Aragon and the Balearic Islands) from patients who meet the inclusion criteria and to whom the characteristics of the study will be explained. Patients will be recruited by GPs working in these PC centres until the required sample is completed, with a quota of 100 patients assigned to each centre. The inclusion and exclusion criteria are given in Table 1.

**Table 1 Tab1:** Inclusion and exclusion criteria

Inclusion criteria	Exclusion criteria
Minimum age of 18 years	Any diagnosis of a disease that may affect the central nervous system (brain condition, traumatic brain injury, dementia, etc.)
DSM-5 diagnosis of Major Depression or persistent depressive disorder, mild or moderate depression expressed as a score lower than 14 in the Patient Health Questionnaire (PHQ-9)	Other psychiatric diagnoses or acute psychiatric illness (substance dependence or abuse, history of schizophrenia or other psychotic disorders, eating disorders, etc.), except for anxiety disorder or personality disorders
Ability to understand oral and written Spanish	Any medical, infectious or degenerative disease that may affect mood
Willingness to participate in the study and signing informed consent	Presence of delusional ideas or hallucinations whether consistent or not with mood
Duration of depressive symptoms 2 months or more	Suicide risk
Diagnosis of one of the following two conditions: - Type 2 Diabetes (Diagnosis according to criteria of the American Diabetes Association, ADA) - Lower back pain (Diagnosis of non-specific chronic low back pain according to the definition established by the CPG COST B-13 with a duration of at least 6 months)	
Possession of and ability to use a computer, an Internet connection and a mobile phone	

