### Recruitment

Participants will be recruited in PC settings by participating GPs from patients fulfilling study criteria. When potential patients are identified by a GP, the characteristics of the study will be explained to them, and if the patients are interested in participating, they will be asked to sign an informed consent. The GPs will complete referral forms, indicating that the patients meet the criteria and will provide a brochure to present the study and an information sheet. The GPs will send the referrals and the patients’ signed consent forms by e-mail to the local researcher. The assessor researcher will contact the participants to agree on the established evaluation times. Some patients may prefer to postpone their decision to participate in the study, in which case they will be provided with information about the study by their GPs and how to contact the research team (by phone, email, or by leaving their information on the website).

The assessor researcher will clarify any doubts, ensure that the participants have read the information about the study, and make sure that they have understood the two experimental conditions. Then the assessor will determine their inclusion in the study from the psychological tests and biological variables related to the inclusion criteria before contacting an independent researcher to implement randomization. This researcher will be unaware of the characteristics of the study. Recruitment will be done consecutively until the final sample sizes are reached.

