### Randomization, allocation and masking of study groups

At such a time, the assessor will collect the baseline data and contact a person independent of the research group to perform the individual randomization and inform the assessor of a code that corresponds to the type of treatment (unknown by the assessor) and send it to the researcher with the baseline data. Another independent person will do the data monitoring with a general practitioner. The randomization will be conducted by blocks of patients from the three PC centres, with 100 patients selected from each centre so that 150 patients are randomized into each of the two arms. Participants agree to their inclusion before finding out the treatment to which they will be allocated. All participants will be free to withdraw from the treatment at any time.

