### Analysis strategy

#### Analysis of clinical efficacy

Intention-to-treat and per-protocol analysis will be used. Analysis will include the description and ‘head-to head’ comparison between the two groups. Descriptive statistics of the included variables (mean and 95% confidence interval for normally distributed quantitative variables; and median and interquartile range for abnormally distributed quantitative variables) will be performed. To confirm the main hypothesis, all variables will be compared (t0-tk) using an analysis of variance (ANOVA) and post-hoc tests or Kruskal-Wallis non-parametric tests. Finally, more sophisticated multivariate analysis, including multilevel regression, will be used. The effect size of improvement and the number needed to treat (NNT) in each arm will be estimated.

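### The Instruments section places baseline after randomization, against the rest of the article; if followed, patients could give their online self-report baselines knowing their arm

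*Protocol article*

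**What the plan says.** The protocol article describes the timing of baseline in several places.

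- **Instruments:** "Patients will be assessed at baseline (post-randomization), after the treatment, and at 3-month and 6-month follow-ups".
- **Randomization, allocation and masking of study groups:** "the assessor will collect the baseline data and contact a person independent of the research group to perform the individual randomization". The treatment code that comes back is then passed to the researcher together with the baseline data.
- **Recruitment:** the assessor settles inclusion from the "psychological tests and biological variables related to the inclusion criteria before contacting an independent researcher to implement randomization".
- **Setting and study sample, Table 1:** one inclusion criterion is "mild or moderate depression expressed as a score lower than 14 in the Patient Health Questionnaire (PHQ-9").
- **Main outcome:** the PHQ-9 is administered on four occasions, namely baseline, post-treatment, 3 months and 6 months.

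On who knows the allocation, the randomization section says "Participants agree to their inclusion before finding out the treatment to which they will be allocated". Instruments adds "The assessor will be blind to the type of treatment that will be administered to patients", and GPs are to be kept blind where possible. No blinding of patients is described.

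On use of the baseline, Analysis of clinical efficacy says "all variables will be compared (t0-tk"), by ANOVA or Kruskal-Wallis. In Main outcome, the PHQ-9 and Roland-Morris components are the percentages of patients whose score falls by at least 2 points.

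**The concern.** A baseline is a fair reference only if allocation cannot have influenced it. Here patients learn whether they will receive two face-to-face sessions and six online modules, and most of the scales are their own reports. Under the order given in Instruments, a patient could complete the baseline forms already knowing the arm. Disappointment in one arm, or hope in the other, would then enter t0 and be carried into every change score built on it.

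Table 2 makes this a practical possibility. At baseline the PHQ-9, MINI, sociodemographic data and service-use inventory are collected by Researcher A by telephone. FPS-R, Roland-Morris, SF-12, EQ-5D-3L and OFS are collected online. The table has a single baseline time point and does not say whether the online forms come before or after the randomization call. Two sites could follow two different orders and both be complying with the article.

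**Working it through.** The plan gives no figure for this point, so the check is a reading of the sections against each other, followed by the algebra of a shifted baseline.

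**1. Which order does the article support?**

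| Section | Order implied |
|---|---|
| Instruments | randomization, then baseline |
| Randomization, allocation and masking | baseline, then randomization; baseline data already exist when the code is passed on |
| Recruitment | eligibility tests, then randomization |
| Table 1 | PHQ-9 score needed for eligibility, hence before randomization |
| Main outcome | PHQ-9 taken four times |

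The PHQ-9 count decides the matter for that scale. One baseline plus three follow-ups makes 1 + 3 = 4 administrations. If the eligibility score were separate from the baseline score, there would be 1 + 1 + 3 = 5. The stated four leave no room for a second PHQ-9 after randomization, so the eligibility score has to be t0. Only the parenthesis in Instruments points the other way.

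**2. Which measures are exposed if Instruments is followed?**

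- *PHQ-9 and MINI:* needed for eligibility and, in Table 2, taken by Researcher A by telephone at baseline (the PHQ-9 entry reads "Researcher A phone Online (follow-up sessions^a"). A score before randomization exists. Exposure is low, although the article never says outright that this score is t0.
- *HbA1c:* a laboratory value, little open to reporting bias. Its criterion of 7 or below needs no baseline; the alternative, a fall of 0.50, does.
- *FPS-R, Roland-Morris, SF-12, EQ-5D-3L, OFS:* online self-report, not tied to eligibility in the article. These are exposed. FPS-R and Roland-Morris belong to the primary composite, for back-pain patients. EQ-5D and SF-12 feed the utility scores.

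**3. How would a shift enter the result?**

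Take a scale on which higher is worse. Let s_I and s_C be the mean shifts in reported baseline caused by knowing the arm (intervention and control). Improvement is t0 − tk.

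- *Change score:* estimated difference in improvement = true difference + (s_I − s_C).
- *Baseline-adjusted, with slope β on baseline:* the bias is β × (s_I − s_C). It is smaller when β is below 1, but not removed.
- *Roland-Morris responder:* a patient whose reported baseline is moved by s counts as a responder when (t0 + s) − tk ≥ 2, that is, when the undistorted fall is at least 2 − s. The responder percentage changes, but not one for one with s.
- *QALYs by area under the curve:* if the curve starts at baseline, the shifted utility enters the area directly.

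**4. Direction.** Disappointed controls report worse baselines (s_C > 0). Hopeful intervention patients report better ones (s_I < 0). Either makes s_I − s_C negative, so a change-score analysis would understate a benefit. For an unadjusted QALY area that starts at baseline the sign reverses, because a lower control utility lowers the control area. Other reactions to allocation could reverse either sign.

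**5. Size.** The documents contain nothing from which s_I or s_C could be obtained. If both are zero, or equal, there is no bias.

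**The case against.** The strongest reply is that this is a slip in one parenthesis and that the trial will measure baseline first, as its other sections say. Post-randomization is also not the same as post-disclosure: the code returned to the assessor is uninformative to the assessor, and the article does not say when patients learn their arm relative to the online forms. The flowchart, which is not shown, may make the sequence clear. All of this is fair, and it is why the point is about a possible bias and not an established one. It does not remove the contradiction, since the two sentences conflict whatever the flowchart shows.

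Three stronger readings are tempting and are not supported:

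- *Every t0-tk comparison is biased.* The PHQ-9, which all patients share, and the MINI are needed before randomization, and HbA1c is a laboratory value.
- *The false-positive rate rises by a calculable amount.* Any such figure needs an assumed shift and an assumed change-score SD on a continuous scale, whereas the primary components are responder percentages. With disappointed controls or hopeful intervention patients, a change-score error would mostly count against the programme.
- *Patients who leave on learning their arm have no baseline.* Their eligibility data exist already; at most the online forms would be missing.

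**Conclusion.** The contradiction is certain: Instruments places baseline after randomization, and the randomization, recruitment, eligibility and outcome sections together place it before. The sentence in Instruments is the one to change.

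The consequence is conditional. Bias arises only if the Instruments order is followed, patients already know their arm when they complete the forms, and this moves answers differently in the two arms. It is then confined mainly to the online self-report measures: the back-pain part of the primary composite, the SF-12, EQ-5D-3L and OFS changes, and the QALYs. Its size cannot be derived from the documents and its direction is uncertain. The correction is still worth making, because a baseline given after disclosure cannot be recovered in the analysis, and adjusting for it does not remove the distortion.

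**What to change.** 1. In Instruments, replace post-randomization with pre-randomization.
2. State that the PHQ-9 score used for eligibility is the t0 score.
3. State that all baseline instruments in Table 2, including the online forms and HbA1c, must be complete before the independent person is contacted for allocation.
4. If any measure has to be taken later, name it, and do not use it as the baseline for change scores or as a covariate.

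The cost is a one-line amendment and a completeness check before the randomization call. The sample size does not change.

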#### Main outcome

According to the objectives of the study, the primary outcome will be a composite that considers the following variables:

Depressive symptom severity will be assessed via the Patient Health Questionnaire (PHQ-9) [40] using the Spanish validated version [41]: Percentage of patients with reduction ≥2 points. The PHQ-9 [40], validated Spanish version [41] is one of the questionnaires that assess the intensity of depression most widely used in pharmacological and psychological studies. It is a brief and self-applied scale whose objective is to help diagnose depression (DSM-IV criteria) and determine its severity. Similarly, it is also useful to monitor changes experienced by patients over time. It will be taken four times: at baseline, post-treatment, and at 3-month and 6-month follow-ups.

Control of diabetes will be measured by VR d = glycosylated haemoglobin (% ≤ 7 or % with a decrease of 0.50 baseline), HbA1c, fasting capillary blood glucose, weight (kg), height (cm), waist circumference (cm), and abdominal diameter (cm).

Pain intensity and physical limitation will be measured. Pain intensity will be assessed via the Faces Pain Scale – Revised (FPS-R) [42], a self-report measure in which the patient scores the chosen face with 0, 2, 4, 6, 8, or 10, counting from left to right, where 0 = no pain, and 10 = very much pain. Disability will be assessed via Roland-Morris Scale [43]: This scale is designed to reliably determine the level of physical disability resulting from non-specific low back pain. In this regard, ‘physical disability’ is defined as the limitation in the performance of daily activities between 0 (absence of disability for back pain) and 24 (maximum possible disability). A change in score only has clinical relevance if it is of 2 or more points, although the optimal threshold is between 3 and 4 [44–46]. VR d = % with decrease ≥2 points.

The composite would be weighted to give 1/3 or 1/2 to each of the main measures of depression, diabetes and pain, obtaining an aggregate score. The calculation of the weighting of the composite variables would be performed by means of multiple regression.

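### The PHQ-9 is taken by phone at baseline but online at every follow-up, so each change score in the depression component of the primary outcome crosses two modes of administration

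*Protocol article*

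**What the plan says.** Table 2 (Instruments) schedules the PHQ-9 at baseline and at the follow-up sessions, and its last column reads "Researcher A phone Online (follow-up sessions^a"). The table footnote defines those sessions: "Follow-up sessions: post-treatment, 3 and 6 post-treatment months". The natural reading is phone at baseline and online afterwards. The service-use row supports it, because it too pairs each mode with its own time point.

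The Main outcome section describes the PHQ-9 this way: "It is a brief and self-applied scale whose objective is to help diagnose depression". The depression part of the composite primary outcome is scored as "Percentage of patients with reduction ≥2 points".

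The pain, disability, SF-12, EQ-5D and openness-to-the-future questionnaires are listed as online throughout, and the service-use inventory is by phone at both of its time points. The PHQ-9 is the only instrument in Table 2 whose mode changes between baseline and follow-up.

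The Analysis of clinical efficacy section plans a comparison of change from baseline between the two groups. It also plans an effect size of improvement and an NNT for each arm.

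**The concern.** A change score is interpretable as change in the patient only if both measurements are taken in the same way. Here the baseline is spoken to a researcher on the phone and every later score is self-completed online. If patients report more or fewer symptoms to an interviewer than on a screen, that gap is added to every PHQ-9 change in the trial.

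The threshold makes this matter more. A 2-point fall is small, so a mode difference of even 1 point is half of what a patient needs to count as a responder. The pain and disability measures are combined with the PHQ-9 in the same composite and carry no such shift. At stake are the responder rates and within-arm improvements that readers will quote, and, to a smaller degree, the responder difference and NNT.

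**Working it through.** **The plan's own figure.** The Sample size section uses 0.5 SD, 80% power and 5% significance (sidedness not stated; two-sided reproduces it). n per group = 2 × (1.960 + 0.842)² / 0.5² = 62.8, so 63. Four groups give 4 × 63 = 252, and 252 / 0.85 = 297, close to the stated 300. The figures reproduce, and this point does not change them.

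**Effect of a common mode shift on means.** Let s be the number of points by which online scores run below phone scores. Observed fall = true fall + s in both arms. Between-arm difference in mean fall = (μ_int + s) − (μ_iTAU + s) = μ_int − μ_iTAU. The shift cancels.

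**Effect on responder rates.** The documents give neither a change SD nor a mode effect, so these inputs are assumptions:
- change SD 4.5 and iTAU mean fall 2 points;
- intervention mean fall 2 + 0.5 × 4.5 = 4.25 (the 0.5 SD is the plan's design effect);
- approximately normal change; as PHQ-9 scores are integers, a fall of at least 2 corresponds to a cut at 1.5.

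Responder rate = P(Z > (1.5 − μ − s) / SD).

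| Shift s | iTAU | Intervention | Difference | NNT = 1/difference |
|---|---|---|---|---|
| 0 | P(Z > −0.111) = 54.4% | P(Z > −0.611) = 72.9% | 18.5 points | 5.4 |
| +1 (online lower) | P(Z > −0.333) = 63.1% | P(Z > −0.833) = 79.8% | 16.7 points | 6.0 |
| −1 (online higher) | P(Z > 0.111) = 45.6% | P(Z > −0.389) = 65.1% | 19.6 points | 5.1 |

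A 1-point shift moves the iTAU rate by about 9 points and the intervention rate by 7 to 8. The difference moves by 1 to 2 points.

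**Effect on within-arm improvement.** Standardized mean fall = (μ + s) / SD. For iTAU this is 2/4.5 = 0.44 with no shift, 3/4.5 = 0.67 at s = +1 and 1/4.5 = 0.22 at s = −1. For the intervention arm it is 0.94, 1.17 and 0.72. Each arm moves by 1/4.5 = 0.22 SD; the gap stays at 0.5 SD.

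**Sensitivity to the assumptions.** With SD 5 and an iTAU fall of 2 points, the rates are 54.0% v 72.6% with no shift (18.6 points, NNT 5.4). At s = +2 they are 69.1% v 84.1% (15.0 points, NNT 6.7). Over SDs of 4 to 6, iTAU falls of 0 or 2 points, and shifts from −2 to +2, the responder difference stays between 13.6 and 19.7 points.

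**The case against.** The strongest reply is that the trial's hypothesis is a comparison between randomized arms and that both arms change mode identically. This stands for the difference in mean change, which a common shift leaves untouched, and largely stands for the responder difference. It does not protect each arm's responder rate or effect size of improvement, which absorb the shift in full.

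A second reply is that the size rests on assumed inputs and that nothing shown demonstrates a mode effect. That is fair: the figures illustrate sensitivity and do not estimate bias. The mode change itself is fixed in Table 2, so it is not a detail left to a fuller document.

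A third is that phone administration at entry, alongside the diagnostic interview, is a workable way to screen. It is, and eligibility is settled before allocation, so any phone effect on entry falls on both arms alike. The difficulty lies in reusing the screening score as the outcome baseline.

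Two stronger readings are tempting and should be resisted:

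- **A biased treatment comparison.** This would need the mode effect to differ by arm. Intervention patients use an online programme for 8–12 weeks and iTAU patients do not, so a difference is conceivable, but the documents neither show nor exclude one.
- **The same flaw in HbA1c.** Table 2 reads "Glycosylated haemoglobin Diabetes control Baseline and follow-up sessions^a^ Online": one entry for all time points, so there is no change of mode. A reader might infer that patients type in their own values. The documents do not say so. The word could mean the route of data entry, and the Recruitment section has the assessor use biological variables to decide inclusion. The source of a laboratory value is also detail that an article may leave to the full protocol. The glucose and body measures have no row in Table 2, so no mode is assigned to them to contradict.

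**Conclusion.** The point holds for the PHQ-9 alone. Table 2 fixes a change of mode between baseline and every follow-up for a scale that the article itself calls self-applied, and the depression component is scored on change across that break. Per-arm responder rates and within-arm effect sizes will mix true improvement with any phone-versus-online difference. On the assumed inputs, a 1-point shift is worth 7–9 percentage points in each arm's responder rate and 0.22 SD in each arm's improvement. The randomized difference in mean change is unaffected by a common shift, and the responder difference moves by only 1–2 points.

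These sizes depend on the assumed SD, mean fall and shift, none of which the documents supply. This is a modest design weakness worth correcting because the correction is cheap; it is no threat to the main between-arm comparison. The HbA1c entry is at most a table cell to clarify and forms no part of the finding.

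**What to change.** Add the PHQ-9 to the online baseline battery that patients already complete, before randomization. State in Table 2 and in the Main outcome section that this online score is the baseline for the primary outcome, and that the phone PHQ-9 serves eligibility only.

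This also requires reconciling the timing of baseline. The Instruments section places it after randomization, whereas the Randomization section has the assessor collect baseline data and then request allocation. The online PHQ-9 should be fixed to the earlier point, before the allocation is known.

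The cost is nine extra items, a few minutes per patient. The sample size and the follow-up schedule do not change. When Table 2 is revised, a short note saying whether the HbA1c entry refers to the source of the value or to the route of data entry would remove that ambiguity.
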